## Abstract

**Background:**

Musculoskeletal disorders (MSDs) constitute a major occupational health problem in the working population, substantially impacting the quality of life of employees. They also cause considerable economic cost to the healthcare system, with, notably, the reimbursement of treatments and compensation for lost income. MSDs manifest as localized pain or functional difficulty in one or more anatomical areas, such as the cervical spine, shoulder, elbow, hand, and wrist. Although prevalence varies depending on the region considered and the method of assessment, a prevalence of 30% is found in different epidemiological studies. The disease needs to be prevented, not only for medical and economic reasons, but also for legal reasons, owing to the requirement of assessing occupational risks. The strategy envisaged may thus revolve around active, multimodal prevention that has employees fully involved at the heart of their care. Although physical exercise is widely recommended, few studies with a good level of evidence have enabled us to base a complete, well-constructed intervention on exercise that can be offered as secondary prevention in these disorders.

**Methods:**

A prospective, multicenter, comparative (intervention arm vs. control arm), randomized (immediate vs. later treatment) study using Zelen’s design. This study falls under active prevention of MSDs of the upper extremities (UE-MSDs). Participants are workers aged between 18 and 65 years with latent or symptomatic MSDS, with any type of job or workstation, with or without an history of sick leave. The primary aim is to show the superiority at 3 months of a combination of spa therapy, exercise, and self-management workshops for 6 days over usual care in the management of MSDs in terms of employee functional capacity in personal and professional daily life. Secondary aims are to assess the benefit of the intervention in terms of pain, quality of life, and accumulated duration of sick leave.

**Discussion:**

This randomized controlled trial is the first that will aim to evaluate multidisciplinary management of UE-MSDs using nonpharmacological treatment combining exercise, self-management, and spa therapy. The originality of this intervention lies, in its short, intensive format, which is compatible with remaining in work; and in its multidisciplinary approach. This trial has the potential to demonstrate, with a good level of evidence, the benefits of a short course of spa therapy combined with a personalized self-management program on the functional capacity, pain, and quality of life of employees in their daily life.

**Trial registration:**

Clinical trial.gov NCT02702466 retrospectively registered.

**Protocol**: Version 4 of 9/10/2015.

**Electronic supplementary material:**

The online version of this article (doi:10.1186/s12891-016-1353-8) contains supplementary material, which is available to authorized users.

## Background

Musculoskeletal disorders (MSDs) constitute a major occupational health problem in the working population, substantially impacting the quality of life of employees [1]. They also cause considerable economic cost to the healthcare system, [2]. MSDs pose difficulties for companies as well, including loss of productivity, accumulated sick leave, and employee absenteeism [3].

The term MSD currently lacks consensus. Both degenerative and inflammatory diseases can define this term [1]. MSDs manifest as either pain or functional difficulty in one or more anatomic areas [4]. Although prevalence varies depending on the regions considered and the methods of evaluation, a prevalence of 30% is found in different epidemiological studies [5]. MSDs of the upper extremities (UE-MSDs) represent two thirds of MSDs, because the upper limbs are at greater risk, and because of exposure to the offending economic sectors that are the supermarket sector, the food industry, and manufacturing companies [6]. Regardless of their location, MSDs may become chronic and lead to long-term disability. Risk factors may be external, involving repetitive biomechanical constraints [7] aggravated by stress, psychosocial factors, and work organization [8]. All these factors interact with each other and may contribute to worsening the pain or impairment. They are also intrinsic to the individual, including age and length of time in the position. Women are more often affected than men [9].

The disease needs to be prevented, not only, of course, for medical and economic reasons, but also for legal reasons, owing to the requirement of assessing occupational risks [10]. Primary prevention is mostly initiated by the company through ergonomic and organizational actions on occupational constraints, but it is far from sufficient. The actual impact of primary prevention continues to be debated in the literature [11].

The strategy envisaged may then revolve around active, multimodal secondary prevention that has employees fully involved at the heart of their care.

Performing exercises or a physical activity reduces MSD-related pain and impairment [12] while also limiting the increase in the risk of morbidity and mortality observed in this kind of population [13]. Although physical exercise is widely recommended, few studies with a good level of evidence allow us to base a complete, well-constructed intervention on exercise that can be offered as secondary prevention of these disorders [14].

Current recommendations for managing chronic pain highlight the benefits of multidisciplinary programs that combine various nonpharmacological treatments. These can potentiate each other to augment their benefits and prolong their positive effects over time [15].

Different studies have shown that self-management has a positive impact in the approach to MSD-related pain and incapacity [16]. The management of stress and pain through sophrology sessions is an additional asset in the therapeutic arsenal for this chronic disorder [17].

Spa therapies have long been used in the management of various rheumatological disorders like osteoarthritis, rheumatoid arthritis, or ankylosing spondylitis [18]. Another study has shown the benefit of balneotherapy on symptoms and quality of life in the management of fibromyalgia, notably by offering a combination of spa therapy, physical exercise, and self-management [19].

To our knowledge, the physical exercise–spa therapy combination has not been specifically studied in the area of UE-MSDs.

### Study objectives

This study falls under active UE-MSD prevention. Its primary aim is to show the superiority at 3 months of a combination of spa therapy, exercise, and self-management training for 6 days over usual care in the management of MSDs in terms of employee functional capacity in personal and professional daily life.

Secondary aims are to assess the benefit of the intervention in terms of pain, quality of life, and accumulated duration of sick leave.

This may lead to the possibility of proposing an alternative to conventional MSD treatment. The objective is to keep employees in work; the study design does not require sick leave. Decreased long-term use of analgesics is expected as well as a control of the unfavorable course of the MSDs. A resurgence in pain and fatigue immediately after the week of treatment is expected to be a possibility.

## Methods

### Subject selection

Recruitment is preferably by posters, media and occupational health services. Following a double assessment (knowledge of the occupation and health status of employees), occupational physicians are the best placed to identify and recruit employees potentially eligible for the study. A more conventional method of recruiting during consultation will also be conducted by general practitioners who have agreed to participate in the study (Fig. 1). Recruiting locally is a necessity because the study targets working people. Thus, patients may carry out the treatment before or after work and return home daily.

**Fig. 1 Fig1:**
[figure not shown]
Flow chart

### Selection criteria

#### Inclusion criteria

Participants are workers with latent or symptomatic MSDs according to the SALTSA European consensus/INRS (French occupational health and safety agency) [20] with a value on the Nordic questionnaire strictly above 2/10 [21]. They are aged between 18 and 65 years, have or have not a history of sick leave, and are covered under national health insurance. No restriction was made regarding type of job or workstation.

#### Exclusion criteria

Workers who are contraindicated to spa therapy or who underwent spa therapy within the last 12 months are not included. Nor are people with behavioral disorders or comprehension difficulties that make assessment impossible (Table 1).

**Table 1 Tab1:** MUSKA study eligibility criteria

Inclusion criteria
-Latent or symptomatic UE-MSD according to the SALTSA European consensus/INRS (French occupational health and safety agency) with a score on the Nordic questionnaire >2
-With or without a history of sick leave and working at the time of inclusion
-Age: >18 years <65 years
-Patient covered under national health insurance (person insured or dependent)
-Patient has given informed written consent to participate in the study
Non inclusion criteria
-Contraindication to spa therapy:
Unstable angina
Myocardial infarction within the previous 6 months
Cerebrovascular accident within the previous 6 months
Recent thrombophlebitis
Attack of inflammatory rheumatism
Progressive cancer
Vascular surgery within the previous 6 months
-Course of spa therapy within the previous 12 months
-Behavioral disorders or comprehension difficulties making assessment impossible

The research may be discontinued early if a contraindication to spa therapy or issues relating to participant availability arise. No exclusion period is planned in this study. No adverse effect is expected. Before each spa therapy session, the contraindications described in the non-inclusion criteria will be checked.

Travel expenses arising from participation in the study will be fully reimbursed at a fixed rate.

### Instruments

The primary endpoint is the score on the Quick DASH scale at 3 months. The Quick DASH (Disability of Arm-Shoulder-Hand) is a self-administered questionnaire which measures the physical disability and symptoms for all upper limb disorders in an heterogeneous population and for acute as well as chronic disorders [22]. It contains various domains such as handicap, activity of daily living, pain during activities, strength. It has good psychometric properties with a Cronbach’s alpha coefficient of 0.89 and an intra-class correlation coefficient of 0.94 which suggests excellent test-retest reliability. We assessed functional capacity monthly over 6 months.

Secondary endpoints are:The areas of pain and intensity of the discomfort or pain are assessed using the Nordic questionnaire [21] and a numerical pain scale.Overall psychological status is assessed using the Hospital Anxiety and Depression Scale by Zigmond and Snaith [23].The SF-36 questionnaire is used for patient quality of life [24].Duration of sick leave accumulated during the study period.Use of analgesics.

### Research design

A prospective, multicenter, comparative (one intervention arm vs. one control arm), randomized (immediate vs. later treatment) study using Zelen’s design [25]. Workers randomized to the intervention group will be given a short, intensive, standardized spa therapy treatment during the following month. The intervention will be offered to control-group subjects at least 3 months later. The total duration of participation in the study for patients is 6 months. The centers were Clermont-Ferrand University Hospital/Royat spa center, Nîmes and Montpellier Hospital/Balaruc spa center.

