**Fig. 2 Fig2:**
[figure not shown]
Self administered questionnaires

Quantitative adherence (number and duration of sessions) and qualitative adherence (type and way of performing the intervention) will be systematically evaluated using monthly follow-up self-administered questionnaires [27, 28].

The assessment of endpoints on day 6 and then monthly over 6 months will be conducted by sending self-administered questionnaires by mail. Reminders and follow-up will be by mail and by telephone calls if necessary.

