The various people in charge of the spa therapy who are responsible for conducting the intervention in this study, have more than 3 years of clinical experience and have been specifically trained in implementing the protocols by means of a detailed handbook that precisely describes each intervention illustrated with photographs and diagrams from the video program given to workers [27].

During the inclusion visit, control-group workers will be given the same folder as the intervention group, with the seven exercise sheets and USB key. The workers are not given guidance on the performance of any exercise that may have been determined by the conduct of the clinical examination. They will perform home program (exercises and relaxation) during the first three months and then the spa therapy of 6 consecutive days identical to the intervention group.

Intervention and control-groups workers will receive unrestricted pharmacological or non-pharmacological usual care from their physicians or specialists, such as analgesics, physiotherapy or orthosis, over 6 months. However, any medication taken during or after the intervention must be declared and reported in the patient follow-up questionnaires.

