#### Statistical analysis

Statistical analysis will be conducted on the intention-to-treat population using Stata software, V.13 (StataCorp, College Station, Texas, USA). A two-sided P value of less than 0.05 will be considered for statistical significance. Baseline characteristics will be presented for each randomized group as the mean ± standard deviation or median (interquartile range) according to the statistical distribution for continuous data, and as the number of patients and associated percentages for categorical parameters. Comparisons between randomized groups will be analyzed using the Chi2 or Fisher’s exact test for categorical variables and the Student t-test or Mann-Whitney’s test for quantitative parameters, with normality verified by the Shapiro-Wilk test and homoscedasticity by the Fisher-Snedecor test (notably for primary outcome QUICK DASH scale at 3 months). Primary analysis will be completed using (1) ancova taking into account baseline QUICK DASH as covariate as recommended by Vickers and Altman [29] and (2) linear regression model in multivariate context. Covariates used for adjustment will be fixed according to (i) univariate results and (ii) clinical relevance including (use of analgesics) stratification factors. Results will be expressed as effect sizes and 95% confidence intervals. Regarding the analysis of repeated measures, random-effect models (linear or generalized linear according to the statistical distribution of dependent variables) will be performed, as usually proposed, to study the fixed-effects group, time points, and “group x time” interaction, taking into account between- and within-subject variability. The impact of covariates (as observance) will be also studied. A sensitivity analysis will be performed to study the impact of missing data; when appropriate, they will be handled in accordance with the estimation method developed by Verbeke and Molenberghs [30].

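### Sick leave is accumulated over 6 months although controls are offered the same spa course after month 3, so the contrast is immediate versus delayed spa, not spa versus usual care

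*Protocol article*

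**What the plan says.** - **Design.** Under Research design, the intervention arm receives a "short, intensive, standardized spa therapy treatment during the following month". For controls, "The intervention will be offered to control-group subjects at least 3 months later". The same section states: "The total duration of participation in the study for patients is 6 months".
- **What controls receive.** Intervention protocol says of the control arm: "They will perform home program (exercises and relaxation) during the first three months and then the spa therapy of 6 consecutive days". It describes that course as identical to the intervention arm's.
- **Sick leave.** Instruments lists as a secondary endpoint: "Duration of sick leave accumulated during the study period". Study objectives names accumulated sick leave among the secondary aims, as a measure of the intervention's benefit. The primary aim there is superiority over usual care.
- **Other windows.** QuickDASH at 3 months is the primary endpoint and the only endpoint tied to month 3. Conduct of the study sets assessments at day 6 and then monthly to month 6.
- **Longitudinal analysis.** Under Statistical analysis, "random-effect models (linear or generalized linear according to the statistical distribution of dependent variables) will be performed" with group, time point and group-by-time effects. No cut at month 3 is stated, nor any term for control-arm spa exposure.

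**The concern.** Taken together, these statements define a secondary endpoint whose counting period runs past the point at which controls may be treated. Until then the arms differ as the objective requires. Afterwards, for every control who accepts, both arms have had the spa week, and what remains is a difference in timing. Adding the two periods gives a figure that answers neither question cleanly. The section on avoiding bias judges contamination unlikely because the programme is not available outside the study; it does not discuss the study's own offer to controls.

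At stake is the reading of a named secondary aim. A real reduction in sick leave during the randomised comparison with usual care could look about half as large, in relative terms, and be reported as absent. An overall group effect from the random-effect models carries the same risk if it is averaged over all six months and presented as spa versus usual care.

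**Working it through.** **Plan figures.** The protocol gives no effect size or power for sick leave or for the repeated-measures models. Its only sizing concerns QuickDASH at 3 months: difference 12, SD 18, two-sided 5%, power 90%, loss 20%, 75 per arm. From the quantified inputs, n = 2(1.960 + 1.282)² × 18²/12² = 47.3, so 48 per arm, and 48/0.8 = 60. The stated 75 also covers a Hawthorne allowance that is given no number, so it cannot be reproduced exactly. That is a separate matter and is not shown to be an error. For power below I use 75 × 0.8 = 60 evaluable per arm.

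**Assumptions not in the documents.** Spa benefit is constant from the start of follow-up (strictly, the intervention arm is treated at some point in the first month). Treated controls gain the same benefit. A 30% sick-leave reduction is illustrative. The correlation between monthly scores, ρ, is 0.3 to 0.9.

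**1. Sick leave.** Let an untreated participant accrue 1 unit per month and a treated one 0.7.

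Months 1 to 3: control 3.0, intervention 2.1; difference 0.9, reduction 0.9/3.0 = 30%.

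| Months 4 to 6 | Control, 6 months | Intervention, 6 months | Relative reduction |
|---|---|---|---|
| No control spa (reference) | 6.0 | 4.2 | 30% |
| All controls treated at month 3, both arms at the treated rate | 3.0 + 2.1 = 5.1 | 4.2 | 0.9/5.1 = 17.6% |
| Both arms at the untreated rate (benefit confined to months 1 to 3) | 6.0 | 2.1 + 3.0 = 5.1 | 0.9/6.0 = 15% |
| Half of controls treated at month 3 | 3.0 + 3 × 0.85 = 5.55 | 4.2 | 1.35/5.55 = 24.3% |
| All controls treated at month 4 | 4.0 + 1.4 = 5.4 | 4.2 | 1.2/5.4 = 22.2% |
| All controls treated at month 5 | 5.0 + 0.7 = 5.7 | 4.2 | 1.5/5.7 = 26.3% |

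In the second and third rows the absolute difference stays at its 3-month value, 0.9, against 1.8 in the reference row. It is not erased, but the later months add leave, and so variance, without adding difference. With equal monthly variances and correlation ρ, the standardised effect over 6 months relative to 3 months is √[3(1 + 2ρ)] / √[6(1 + 5ρ)]. This is 0.71 at ρ = 0 and 0.50 at ρ = 1.

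**2. Overall group effect on QuickDASH.** With 12 points at months 1 to 3 and full control uptake at month 3, the mean over the six monthly assessments is (12 + 12 + 12 + 0 + 0 + 0)/6 = 6 points. At 50% uptake it is (3 × 12 + 3 × 6)/6 = 9 points. The SD of a mean of m monthly scores is 18√[(1 + (m − 1)ρ)/m]. With 60 per arm:

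| ρ | Power, months 1 to 6, 6 points | Power, months 1 to 3, 12 points |
|---|---|---|
| 0.3 | 81% | 99.9% |
| 0.5 | 67% | 99% |
| 0.7 | 56% | 98% |
| 0.9 | 48% | 97% |

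**3. What is untouched.** A model with time points and a group-by-time interaction yields a separate arm contrast at each month. Those for months 1, 2 and 3 use data from before control spa. The primary endpoint is one of these time points.

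**The case against.** **Immediate versus delayed is a legitimate randomised contrast.** The article openly describes the trial as immediate versus later treatment, and an intention-to-treat comparison to month 6 is valid for that question. This stands: later data need not be discarded or denied a p-value. It does not rescue the sick-leave endpoint as a measure of benefit over usual care.

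**The dilution may be small.** Spa is offered, and at least 3 months later, so its size depends on uptake and timing. Study objectives also foresees possible pain and fatigue just after the spa week, which could temporarily worsen controls after month 3. Both points stand: the direction is likely rather than certain, and the 15 to 18% figure is the full-uptake case.

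**Windows belong in the analysis plan.** This is fair for the repeated-measures contrasts. It is not an answer for sick leave, whose window the article itself fixes.

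Four stronger readings are tempting but not supported:

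- *Every longitudinal estimate is diluted.* The group-by-time model keeps clean contrasts at months 1 to 3. The article does not name a 6-month average as the reported estimate.
- *The interaction is pulled to zero.* Crossover can itself create an interaction.
- *Analgesic use is compared to month 6.* No window is stated for it.
- *The primary endpoint is contaminated by late questionnaires.* Forms are mailed, and "Reminders and follow-up will be by mail and by telephone calls if necessary", so a late return is conceivable. But the text places control spa after the first three months, and no figure in it supports any share of forms completed after spa.

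**Conclusion.** The point holds for accumulated sick leave: as defined, the endpoint mixes time in which spa is compared with usual care and time in which both arms may have been treated. With full uptake at month 3, even accrual and a 30% effect, the relative reduction is roughly halved, to 15 to 18%. With half uptake, or uptake at month 4 or 5, it is 22 to 26%. It holds conditionally for the random-effect models: only a group effect averaged over months 1 to 6 falls, from 12 to 6 points at full uptake. The month 1 to 3 contrasts and the 3-month primary endpoint stand, provided control spa follows the month-3 assessment. The effect size, uptake and correlation figures are assumptions. Because one secondary aim is affected and the primary analysis is not, this should be fixed but is not critical.

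**What to change.** 1. Define the main between-arm sick-leave comparison as leave accumulated from randomisation to month 3, before control spa.
2. State that the longitudinal estimates of spa versus usual care are the group-by-time contrasts up to month 3, not a group effect averaged over six months.
3. Report months 4 to 6, including 6-month sick leave if wanted, labelled as immediate versus delayed treatment.

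The change is one of wording; no additional data are needed if sick leave is recorded on the monthly questionnaires, which the article does not state explicitly. The real cost is a shorter sick-leave window with fewer events and therefore a less precise estimate of total leave. Under the assumptions above the standardised effect is still larger in that window, because the later months add variance but no difference.
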